**Methods/Design:**

Eight universities in four regions in Germany will take part in the study, four serving as intervention and four as delayed intervention control universities (randomly selected within a geographic region). Six hundred students will be recruited at each university and will be asked to complete a web-based survey assessing personal and perceived substance use/attitudes towards substance use at baseline. These data will be used to develop the web-based ‘social norms’-feedback tailored to gender and university. Three months after the baseline survey, students at intervention universities will receive the intervention. Two months after the launch of the intervention, students of all eight universities will be asked to complete the follow-up questionnaires to assess changes in perceptions of/attitudes toward peer substance use and rates of personal substance use.

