### Sample size

The sample size calculation is based on the prevalence for heavy drinking reported in a previous study conducted in Germany with 3307 students [5]. In total, we aim to reach 4800 students at baseline, 600 students at each participating university. We assume a 40 % loss to follow-up five months post-baseline. The sample size will allow an estimation of a difference in the rate of heavy drinking between the intervention and control sites (at follow-up), corresponding to an effect size of 0.2 at the level of p < .05 with 81 % power.

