Referring to this range of substances, students will be asked to report their personal substance use behaviors and attitudes towards substance use and the perceived gender-specific behaviors (*descriptive norm*) and attitudes (*injunctive norm*) of their peers.

Apart from these questions, an adapted version of the CORE Alcohol and Drug Survey Long Form [28] will be used to assess negative consequences of using alcohol or illicit substances (e.g., missing a class or another commitment, unprotected sex, engagement in violent acts). Finally, students will be asked how they heard about the survey (e.g., via email, information during a lecture, social media channel). This will contribute to an improvement in the selection of suitable recruitment channels in future surveys targeting university students. All questions will be referring to a time period of three months prior to assessment. After completing the questionnaire, students will receive the contact information of the researcher who coordinates the study and who can be contacted for project-related questions. Furthermore, they will be informed about local drug counselling services (at their university and available outside the university setting) that can be contacted if they require counselling regarding their personal substance use behavior.

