### Use of a web-based social norms-approach

The implementation of a personalized web-based, gender-specific, normative intervention is the central part of the INSIST-study. We will develop a gender-specific normative feedback for the intervention group (i.e., students enrolled at the four intervention universities) that will be based on previously assessed baseline data regarding descriptive and injunctive norms related to substance use at the respective university. Students from the intervention universities who registered for the study will be invited by email to check their personalized normative feedback approximately two months after the baseline survey opens. Students will be informed that they can access their personalized feedback multiple times. The feedback website will consist of several different main pages that will be accessible via a navigation menu. Each main page will contain information about a different substance (i.e., alcohol, tobacco, cannabis). All main pages will be divided into a personalized feedback and a gender- and university-specific feedback. The personalized feedback will include the individual information regarding own substance use and the perception of use in the peer group (same gender, same university) reported by students. If students do not fill out the respective questions of the baseline questionnaire beforehand, they will be informed that an individual feedback cannot be displayed because of missing data. The gender- and university-specific feedback will visualize the perceived peer substance use (of the majority of students of the same gender, same university) that was estimated by the survey participant. This information will be contrasted with the actual substance use pattern of students of the same gender and same university that was assessed in the baseline questionnaire. These two comparisons will form the *descriptive norms* feedback. Furthermore, students will receive information about the *injunctive norms* of same-gender peers at their universities. This information will be displayed on the feedback website in corresponding information boxes.

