### Follow-up survey and delayed intervention for participants at control universities

The follow-up survey will take place approximately five months post-baseline and the same items will be employed. The only difference will be that students will not be asked in the follow-up survey how they heard about the study but students at the intervention universities will be asked whether they remember the content of the normative feedback. To illustrate the question, an example from the normative feedback will be used. At the end of the study, students at the delayed intervention control universities will be provided access to the intervention.

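### The article gives two launch dates for the feedback; on the abstract's date, one of the three months recalled at follow-up falls before the intervention

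*Protocol article*

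**What the plan says.** Four places in the protocol article bear on the timing.

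- Recall period (Design of the baseline questionnaire): "All questions will be referring to a time period of three months prior to assessment".
- Launch and follow-up in the abstract (Methods/Design). On launch it says: "Three months after the baseline survey, students at intervention universities will receive the intervention". For the second survey it sets this interval from launch: "Two months after the launch of the intervention, students of all eight universities will be asked to complete the follow-up questionnaires".
- Launch in the Methods (Use of a web-based social norms-approach): registered students at intervention universities are "invited by email to check their personalized normative feedback approximately two months after the baseline survey opens".
- Follow-up in the Methods (section on the follow-up survey and the delayed intervention), where the timing is given as: "The follow-up survey will take place approximately five months post-baseline and the same items will be employed". The Sample size section uses the same time point: "We assume a 40 % loss to follow-up five months post-baseline".

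The Quantitative analysis section then evaluates efficacy by comparing use before and after the intervention between the two groups of universities.

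**The concern.** The two accounts agree that follow-up is at month 5 but differ by one month on launch. That month matters because of the recall period. A three-month look-back from month 5 starts at month 2. If launch is also at about month 2, the follow-up answers describe use after the intervention became available. If launch is at month 3, they mix one month of use before launch with two months after it, and the comparison described in the analysis section is not fully what the items measure.

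At stake is the second primary objective, lower substance use at follow-up, for those items whose answer accumulates over the window. The number of occasions on which a student got drunk includes pre-launch occasions directly. The largest number of drinks on a drinking day can be fixed by a single pre-launch day, whatever happens afterwards. Analysis cannot repair this later, because an item that pools three months cannot be split into its parts.

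**Working it through.** **Inputs, all from the article**

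- Recall period R = 3 months (Design of the baseline questionnaire).
- Follow-up F = 5 months post-baseline (Follow-up survey section; Sample size).
- Launch L = 3 months, and launch-to-follow-up gap = 2 months (abstract).
- Launch L = about 2 months (Use of a web-based social norms-approach).

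**Reproducing the stated follow-up time.** Abstract: 3 + 2 = 5 months, which matches the five months in the Methods. The disagreement is therefore about launch, not follow-up.

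**Gap from launch to follow-up (F − L)**

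- Abstract: 5 − 3 = 2 months.
- Methods: 5 − 2 = about 3 months. The article does not state this interval; it follows from the two Methods sections.

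**Share of the recall window before launch:** max(0, R − gap) / R

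- Abstract: (3 − 2) / 3 = 1/3 = 33%. The window is months 2 to 5, with launch at month 3.
- Methods: (3 − 3) / 3 = 0%. The window is months 2 to 5, with launch at about month 2.

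**Sensitivity to the gap**, since the Methods times are approximate:

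| Gap (months) | Share of window before launch |
|---|---|
| 1.5 | 50% |
| 2.0 | 33% |
| 2.5 | 17% |
| 3.0 or more | 0% |

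**Could a baseline field period reconcile the two?** The Methods count from the opening of the survey. A count from the baseline survey cannot begin before it opens. If the abstract counts from closing, its launch lies even later and the gap between the two accounts widens. The one-third overlap does not depend on this point, because the abstract states the two-month gap directly.

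**What the overlap does to a count item.** This rests on an assumption that is not in the article: the effect starts at launch and is constant. Let the monthly rate be λ without the intervention and rλ after launch.

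- Whole window after launch: difference = 3λ − 3rλ = 3λ(1 − r).
- Abstract's timetable: difference = 3λ − (λ + 2rλ) = 2λ(1 − r).
- Ratio = 2/3, so the contrast shrinks by one third.

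For a maximum over the window the direction is the same, but the article holds nothing from which to compute a fraction.

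**Illustration for power.** This further assumes that the planned effect size of 0.2 is the effect under full exposure and that the standard error is unchanged.

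- Two-sided 5% test with 81% power: 1.960 + 0.878 = 2.838.
- Two thirds of that: 1.892, corresponding to an effect of 0.2 × 2/3 = 0.133.
- Power = Φ(1.892 − 1.960) = 47%.

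**The case against.** The strongest reply is that the overlap arises on only one of the two timetables. The Methods, which describe the operation of the study, already give a gap of about three months and no overlap. If they are right, correcting the abstract settles the matter. This stands, and it limits the finding to a contradiction with a conditional consequence. A reader might infer that the trial does count pre-launch use as outcome; the article does not establish that.

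A reader might also infer that power falls to 47%. The article does not support this. The Sample size section describes a difference in heavy-drinking rates between sites at follow-up, "corresponding to an effect size of 0.2 at the level of p < .05 with 81 % power". Read as worded, 0.2 is the difference as measured, so an overlap would not lower the stated 81%; it would mean that a larger underlying effect is needed to produce it. Nor can a figure be built on the 62% three-month heavy-drinking prevalence in the Background. That comes from a different source from the one named for the sample size, and having any heavy drinking in three months is not among the alcohol variables listed for the questionnaire.

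It would also be too broad to say that every use endpoint is diluted. The usual number of drinks per drinking day is a typical-quantity item, and nothing shows that a one-third loss applies to it. Perceived norms, the first primary objective, are not shown to be affected.

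Both arms share the same window, so an overlap weakens the contrast and does not create a false effect. That is correct. It lowers the seriousness but does not remove the problem in a trial meant to detect a reduction.

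Finally, students may open the feedback some time after the invitation. This is true of any fixed follow-up after an email invitation, and aligning the dates would not cure it, so it adds nothing specific here.

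**Conclusion.** The point holds as a stated contradiction with a conditional consequence. The article gives launch at three months and at about two months, with follow-up at about five months in both accounts. With a three-month look-back, one third of the follow-up window precedes launch on the abstract's timetable and none on the Methods timetable. These shares need only the article's own figures.

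If the abstract is followed, the between-arm contrast would be attenuated for use items that count or take a maximum over the window. For counts the attenuation is up to about one third, on the assumption of a constant effect from launch. No power figure can be attached with confidence. The timing should be settled before the follow-up survey opens.

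**What to change.** State one launch time and one follow-up time, and use them in the abstract, in the sections on the questionnaire, the feedback and the follow-up survey, and in the Sample size section. Which launch date is kept is for the investigators to decide. Whichever it is, specify that the follow-up survey opens in both arms no earlier than three months after launch. Write this as a minimum interval and not as an approximate month, since a gap of 2.5 months would already put 17% of the window before launch.

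Keep the follow-up items and the three-month recall period identical to baseline. Shortening the recall period at follow-up would also remove the overlap, but it would break the like-for-like comparison with baseline on which the efficacy analysis relies.

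Cost: if the Methods launch time is kept, text alignment and a firm minimum interval. If the abstract's launch time is kept, follow-up moves from about month 5 to about month 6 (3 + 3), and the 40% loss assumption, now stated for five months, has to be restated for the later time.

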### Use of a web-based social norms-approach

The implementation of a personalized web-based, gender-specific, normative intervention is the central part of the INSIST-study. We will develop a gender-specific normative feedback for the intervention group (i.e., students enrolled at the four intervention universities) that will be based on previously assessed baseline data regarding descriptive and injunctive norms related to substance use at the respective university. Students from the intervention universities who registered for the study will be invited by email to check their personalized normative feedback approximately two months after the baseline survey opens. Students will be informed that they can access their personalized feedback multiple times. The feedback website will consist of several different main pages that will be accessible via a navigation menu. Each main page will contain information about a different substance (i.e., alcohol, tobacco, cannabis). All main pages will be divided into a personalized feedback and a gender- and university-specific feedback. The personalized feedback will include the individual information regarding own substance use and the perception of use in the peer group (same gender, same university) reported by students. If students do not fill out the respective questions of the baseline questionnaire beforehand, they will be informed that an individual feedback cannot be displayed because of missing data. The gender- and university-specific feedback will visualize the perceived peer substance use (of the majority of students of the same gender, same university) that was estimated by the survey participant. This information will be contrasted with the actual substance use pattern of students of the same gender and same university that was assessed in the baseline questionnaire. These two comparisons will form the *descriptive norms* feedback. Furthermore, students will receive information about the *injunctive norms* of same-gender peers at their universities. This information will be displayed on the feedback website in corresponding information boxes.

### Follow-up survey and delayed intervention for participants at control universities

The follow-up survey will take place approximately five months post-baseline and the same items will be employed. The only difference will be that students will not be asked in the follow-up survey how they heard about the study but students at the intervention universities will be asked whether they remember the content of the normative feedback. To illustrate the question, an example from the normative feedback will be used. At the end of the study, students at the delayed intervention control universities will be provided access to the intervention.

### Qualitative research informing the design of the intervention

Focus group discussions with the target group will be held to gather suggestions regarding the suitability of the INSIST-questionnaire and the web-based gender-specific normative feedback. Specifically, German students will be asked questions regarding their opinions on the reference groups used in the questionnaire. In addition, students will be asked who they consider to be a “typical student” and whether they think that their peers can identify with this term. Further, they will be asked to provide their opinion regarding different categories for determining a ‘majority of students’ (e.g., >51 %, or a value between 0–10 or 0–100 of male or female peers at their university). Focus group discussions will be led by a researcher of the INSIST team using a previously developed focus group guide. Attendance of six to ten university students will be intended per focus group discussion. Participants will be recruited using the snowball-method. Researchers leading the focus groups will obtain an informed consent by focus group participants before starting the discussion.

### Analysis strategy

#### Quantitative analysis

Self-other discrepancies in perceptions of substance use and personal substance use behavior will be evaluated by analyzing whether students perceived the substance use of the majority of their peers to be lower/equal/higher than their personal substance use in bivariate analyses. Cross-sectional associations between perceptions of peer substance use and personal substance use at baseline will be analyzed using logistic regression. To evaluate intervention efficacy, substance use pre- and post-intervention among students at intervention universities will be compared to the use reported by students enrolled at delayed intervention control universities. The same approach will be taken for the analysis of changes in the descriptive and injunctive norms related to substance use for the different substances over time. Both analyses will involve bivariate tests and generalized linear models. In addition, structural equation models will be used to assess relationships between changes in norms and substance use behaviors, similar to previous studies investigating efficacy of ‘social norms’-interventions [28]. SAS statistical software [29] will be used to undertake quantitative analyses.

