## Methods

### Study aims

The primary objectives of the INSIST (‘INternet-based Social norms-Intervention for the prevention of substance use among Students’)-study are to evaluate (I) whether misperceptions of peer substance use are reduced as a consequence of participating in the intervention and (II) whether students participating in the intervention report lower rates of substance use at follow-up than those not participating in the intervention. Differences between the estimates (norms and use of substances) of students of the intervention and the control group are used as indicators to measure possible intervention effects.

Secondary objectives of the INSIST-study include:(i)The detailed assessment of self-reported consumption rates of licit and illicit substances in a large sample of German university students;(ii)the adaption of an internationally implemented ‘social norms’-intervention to the needs of German university students using qualitative results of focus group discussions with university students.

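### The efficacy contrast is worded as a follow-up difference in some sections and as a pre/post change in others, and neither the unadjusted bivariate tests nor the generalized linear models are named as decisive; one baseline-adjusted, cluster-respecting model should be

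*Protocol article*

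**What the plan says.** The protocol article describes the efficacy comparison in two ways.

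**As a difference at follow-up.** Objective II under Study aims asks whether "students participating in the intervention report lower rates of substance use at follow-up than those not participating in the intervention". The Sample size section gives power for "a difference in the rate of heavy drinking between the intervention and control sites (at follow-up").

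**As a change.** The main aim at the end of the Background and the Expected results section both speak of a larger reduction in the intervention arm. Objective I asks "whether misperceptions of peer substance use are reduced as a consequence of participating in the intervention". The Quantitative analysis section states that "substance use pre- and post-intervention among students at intervention universities will be compared to the use reported by students enrolled at delayed intervention control universities". It does not say at which time the control students' use is taken. The same approach is applied to changes in norms over time.

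A further sentence under Study aims, "Differences between the estimates (norms and use of substances) of students of the intervention and the control group are used as indicators", gives no time point and fits either reading.

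For both use and norms, the Quantitative analysis section names bivariate tests together with generalized linear models. It does not say which decides efficacy. The baseline and follow-up questionnaires carry the same outcome items in both arms (Design of the baseline questionnaire; Follow-up survey). Allocation is by random selection within four regional pairs of universities (Participants and procedures).

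**The concern.** A follow-up contrast, a change contrast and a baseline-adjusted contrast can give different estimates from the same data, and they have different variances. If the article does not settle which one decides, an unadjusted test and an adjusted model may disagree with no rule to choose between them. The published power also cannot be tied to a particular analysis.

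The design makes this matter. Only eight universities are randomised, and they include a medical school, a university of applied sciences and general universities. Four against four will often differ at baseline by chance. A follow-up-only comparison carries that difference forward. A simple bivariate test of follow-up values cannot take a baseline covariate, and a bivariate test of change scores uses the baseline with a fixed weight of one, which is not the efficient weight.

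**Working it through.** **Inputs from the article.** "we aim to reach 4800 students at baseline, 600 students at each participating university"; "We assume a 40 % loss to follow-up five months post-baseline"; "corresponding to an effect size of 0.2 at the level of p < .05 with 81 % power". Hence 4800 × 0.6 = 2880 students at follow-up, 1440 per arm and 360 per university. The 62% three-month heavy-drinking prevalence is from the Background. It is illustrative only, because it comes from a different source than the one cited for the sample size.

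**Inputs assumed (not in the article).** The ICC; the baseline/follow-up correlation within universities, rw = 0.5; and between universities, rb = 0.5 to 0.7. The effect of 0.2 is taken as a standardised difference.

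**1. The stated 81%.** Ignoring clustering, the standard error is √(2/1440) = 0.0373 and two-sided power is 99.97%. For 81% power, 403 students per arm suffice. The stated figure therefore does not follow from the stated inputs for individual students. An unstated design effect of 1440/403 = 3.57 would explain it, which implies ICC = (3.57 − 1)/359 = 0.0072 (normal approximation). So 81% is not shown to be wrong, only not derivable from the article. I use 0.0072 as the working ICC.

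**2. Chance baseline imbalance.** The SD of true university prevalence is √(0.0072 × 0.62 × 0.38) = 0.041. For the difference between two sets of four, the 95% range is 1.96 × √(2/4) × 0.041 = ±5.7 points. At ICC 0.02 it is ±9.5 points. The target is 9.9 points (62% to 52.1%) if 0.2 is Cohen's h. With sampling error included, the arm difference has SD 0.071 outcome SDs, and the chance that it exceeds 0.1 SD is 16%. Under individual randomisation of the same number it would be 0.7%. These figures ignore the regional pairing, which lowers the imbalance if regions differ.

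**3. Power of the three contrasts.** Variance = (2/4) × [ICC × fb + (1 − ICC) × fw/360], with a two-sided noncentral t test. The factors fb and fw are:
- follow-up only: 1 and 1;
- change score: 2(1 − rb) and 2(1 − rw);
- baseline-adjusted: 1 − rb² and 1 − rw².

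| Contrast, ICC 0.0072 | rb = 0.5, rw = 0.5 | rb = 0.7, rw = 0.5 |
|---|---|---|
| Follow-up only, 6 df | SE 0.0706, 66% | SE 0.0706, 66% |
| Change score, 6 df | SE 0.0706, 66% | SE 0.0595, 80% |
| Baseline-adjusted, 6 df | SE 0.0611, 78% | SE 0.0536, 87% |
| As above plus university baseline mean, 5 df | 74% | 84% |
| As above plus region, 2 df | 44% | 52% |

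The last row assumes that region explains no variance. The 87% is slightly generous for a model with the student's baseline value alone. One common slope of 0.5 would leave a between-university factor of 1 − 2 × 0.5 × 0.7 + 0.5² = 0.55, not 0.51. Capturing the full between-university gain needs the university mean, hence the 5-df row.

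**The case against.** A reader might infer that the trial's aim is follow-up-only throughout and that the analysis ignores baseline. The documents do not support that. The main aim, objective I and the Expected results are worded as change, and the Quantitative analysis section uses pre-intervention data. A pre/post comparison between arms already subtracts a baseline difference. The generalized linear models may carry the baseline value; their covariate list is commonly left to a fuller document, so its absence here is not a finding. All of this stands.

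It also follows that setting the adjusted model against a follow-up-only test, 66% against 87%, overstates the gain. Against a change score the gain is from 66% to 74–78%, or from 80% to 84–87%. Nor does adjustment remove imbalance: in the table it leaves a variance factor of 0.75 (0.0611²/0.0706²) or 0.58 (0.0536²/0.0706²), and unmeasured university differences remain. Regional pairing is another protection already in the design.

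A follow-up-only contrast is also valid under randomisation if clustering is respected, so the cost is chiefly lost precision. Choosing between a change score and baseline adjustment is largely a matter of efficiency.

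What the objection does not answer is that the article itself states two different contrasts and names two kinds of analysis without ranking them. Those are statements in the text, not details left out by condensation.

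**Conclusion.** The concern holds in a limited form. The efficacy contrast needs to be reconciled across the Background, Study aims, Sample size, Quantitative analysis and Expected results sections, and one analysis needs to be decisive. A baseline-adjusted model is the better choice because it uses items already planned in both arms.

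At ICC 0.0072, the gain over a change score is about 4 to 12 percentage points of power, depending on the correlations and on whether the university mean is included. Over a follow-up-only test it is about 8 to 21 points. The direction holds in every case examined, except that adding region on top of the university mean reverses it. The sizes rest on a back-solved ICC and assumed correlations, and the ±5.7 points also rests on a borrowed prevalence and ignores pairing. Confidence is medium. The point is worth correcting before analysis, but it does not show that the planned analysis is invalid.

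**What to change.** 1. State one decisive analysis for use and norm outcomes alike: the follow-up outcome modelled on allocation, adjusted for the student's baseline value of the same item, in a model that respects clustering by university.
2. Label the bivariate tests descriptive.
3. Align the wording of the Background aim, objectives I and II, the power statement, the Quantitative analysis section and the Expected results with that contrast.
4. For binary outcomes, report a marginal difference in rates from the adjusted model. A logistic coefficient would target a conditional odds ratio, which is not the rate difference used in the Sample size section.
5. The university baseline mean may be added, at the cost of one degree of freedom (6 to 5). Region should not be added on top of it, because only 2 would remain.

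The cost is model specification and wording, with no new data. A rule is needed for students with no baseline record, who can occur: the article foresees registered students who have not answered the relevant baseline questions.
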